#### Implementation

Healthcare providers at the facilities in the intervention arm will be given a lead-in time of 20 days following completion of the training, during which they will be provided with on-site support while using the mIRA EDSS to provide ANC. During this time, any errors encountered with the mIRA EDSS will be corrected and updates will be released. After the lead-in time, and the installation of the final version of the mIRA EDSS in the tablets being used in the intervention arm, the healthcare providers will be expected to use the mIRA EDSS to conduct ANC consultations for all pregnant women who visit the facilities. Field research staff will be stationed at the facilities in the intervention arm on rotation during the recruitment period and will conduct monthly monitoring visits to all facilities during the follow-up period.

#### Monitoring

The intervention will be monitored at frequent intervals from the start of implementation after the training, until the conclusion of the trial. Monitoring will consist of in-person monthly visits conducted by field research staff to the facilities in the intervention arm. During these visits to the facilities in the intervention arm, field research staff will fill a monitoring checklist to record hardware and mIRA EDSS software availability and functionality, identify newly posted staff in need of training in the mIRA EDSS, and record indicators of utilization for the process evaluation. Field research staff will document any technical problems with the tablet hardware or mIRA EDSS software and attempt to resolve them during the monitoring visit. Field research staff will explain any new changes made to the application, and ensure that the latest version is downloaded on the tablets. They will be instructed and trained not to intervene if tablets are not being used during ANC consultations and will not provide support if asked for help while conducting an ANC visit observation (but can help after the observation is over).

We will also conduct remote monitoring of mIRA EDSS usage data. Data from the mIRA EDSS will be used to assess the utilization of the intervention by frontline healthcare workers via timing and duration of logins, and the number of mIRA EDSS entries on a given date. The frequency of data upload to the server will be documented. GPS coordinates of the tablet during application use will be used to assess whether data entry is occurring at the facility site. This data will not be shared with the field research staff. Data on the weekly ratio of entries saved vs submitted, the proportion of applicable input fields completed, the proportion of mIRA EDSS recommendations accepted (vs ‘reject/modify’), and the proportion of records prompting a test with the test results recorded in the application will be used to assess the quality of mIRA EDSS utilization and intervention fidelity. We will document additional data on technical support, such as events of application crashes and other technical errors reported to designated mIRA research staff, time taken to resolve queries, or the number of requests received from healthcare providers for help with data editing in the application. This activity will not be used for course correction, beyond maintenance and technical support, during the trial’s implementation period.

### Data collection

Field research staff stationed at or visiting the facilities will conduct ANC observations using an ANC observation checklist to collect the trial outcome data for the women who consented to participate in the trial in intervention and control facilities. This paper-based ANC checklist will be used to record the components of ANC completed by the health care provider during a consultation with pregnant women recruited under the trial. The first ANC observation will be conducted on the day of recruitment (the ‘enrolment visit’). The field research staff will collect contact details from the woman during the enrolment visit and will telephone the woman one week prior to her next scheduled routine ANC visit to confirm her appointment. Field research staff will then make sure to be present at the facility for the pregnant woman’s visit to conduct the second ANC observation. Throughout this time, all information will also be collected from paper-based records such as the ANC, high risk, and referral registers, and the Mother and Child Protection (MCP) cards. All trial outcome data will be collected via the ANC observation checklist (Supplementary file 3) & MCP cards to ensure comparability between arms. A summary of trial outcomes’ data collection, tools, sources and period of data collection has been provided in Table 1, and the CONSORT trial flow diagram is presented in Fig. 5.

**Table 1 Tab1:** Data collection and source

Outcome	Data source	Time
The mean number of the four selected ANC components completed per visit over two visits (8 components) *(primary outcome)*	ANC observation tool	At enrolment visit and next routine ANC visit
The mean number of the four selected ANC components completed at the enrolment visit *(secondary outcome #1)*	ANC observation tool	At enrolment visit
The mean number of symptoms discussed either by the provider asking or the woman volunteering (nausea, vomiting, vaginal bleeding, severe headache, decreased or absent fetal movement, severe abdominal pain, blurred vision) observed over the two visits (*secondary outcome #2*)	ANC observation tool	At enrolment visit and next routine ANC visit
(among participants who said they were experiencing vomiting, vaginal bleeding, severe headache, decreased or absent fetal movement, severe abdominal pain or blurred vision or who were told that they had hypertension in pregnancy, GDM or anaemia) the action taken by the provider in response *(secondary outcome #3)*	ANC observation tool & MCP card	At enrolment visit and next routine ANC visit
The mean number of danger signs the provider tells the women she should return for help (*secondary outcome #4*)	ANC observation tool	At enrolment visit and next routine ANC visit
The proportion of participants were* told* by the provider that they had hypertension in pregnancy, GDM or severe anaemia (*secondary outcome #5*)	ANC observation tool	At enrolment visit and next routine ANC visit
proportion of participants for whom there was a recording of the diagnostic parameters of hypertension, GDM or severe anaemia (*secondary outcome #6*)	MCP card	At enrolment visit and next routine ANC visit
In the enrolment visit, the mean number of 20 components of quality antenatal care delivered *(secondary outcome #7)*	ANC observation tool	At enrolment visit

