### Secondary outcomes

The secondary outcomes are the:Mean number of the four ANC components observed at the enrolment visit.Mean number of the following symptoms discussed with participants (either by the provider asking or the woman mentioning), observed over the two visits: nausea, vomiting, vaginal bleeding, severe headache, decreased or absent fetal movement, severe abdominal pain, and blurred vision.Proportion of providers who took the appropriate action per participant (as recommended by the mIRA EDSS) in response to the aforementioned symptoms (vomiting, vaginal bleeding, severe headache, decreased or absent fetal movement, severe abdominal pain, blurred vision) or reported clinical parameters indicative of PIH, GDM, or severe anaemia.Mean number of the danger signs (severe vomiting, vaginal bleeding, severe headache, decreased or no fetal movement, severe abdominal pain, blurred vision) mentioned to each participant by the healthcare provider for which she is advised to return for help.Proportion of participants with clinical parameters indicative of PIH (SBP ≥ 140 mmHg and DBP ≥ 90 mmHg), GDM (venous blood glucose: fasting > 92 mg/dL, 1 h OGTT > 180 mg/dL, 2 h OGTT > 153–199 mg/dL; glucometer test values: fasting > 92 mg/dL, 1 h OGTT > 198 mg/dL, 2 h OGTT > 168–219 mg/dL) or severe anaemia (< 7 g/dL).Proportion of participants who were told by the provider that they had PIH, GDM or severe anaemia.Mean number of quality ANC components delivered in the enrolment visit. The components (n = 20) are as follows:
tests completed: blood pressure; blood glucose; urinary dipstick; hemoglobin tests;symptom check: nausea; vomiting; vaginal bleeding; severe headache; decreased or absent fetal movement; severe abdominal pain; blurred vision;warning about: severe vomiting; vaginal bleeding; severe headache; decreased or no fetal movement; severe abdominalpain; blurred vision;enquiring about mental health;writing on the woman-held Mother and Child Protection card.

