### Economic evaluation

We will conduct an economic evaluation to estimate the additional costs of the intervention relative to the value of the improved health outcomes achieved by calculating the additional cost of the intervention and the use of resources for providing ANC in the intervention and control arms.

The cost of the enhanced ANC intervention includes the cost of the mIRA EDSS, and the training costs incurred to facilitate the integrated management of patients by healthcare providers. Healthcare resource use will also change if the intervention is successful. While for some women, improved management will avoid some future costs, healthcare resources used by others will increase as a consequence of receiving care that they would not have received in the absence of the intervention. Thus, the net impact might be to either increase or decrease costs. The improved health outcomes will be estimated using trial data on the number of ANC components received by women; the proportion of women identified with GDM or PIH; the proportion of women with GDM or PIH whose blood sugar and pressure are controlled to recommended targets (in both the control and intervention arms). This information will be combined with data from the literature to estimate the additional QALYs generated by the intervention. The final step is to combine the changes in resource use and the changes in health outcomes in a single measure that can potentially be compared with the cost-effectiveness of other interventions for this patient group, or other patient groups.

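### Secondary outcome #3 (appropriate action) has two conflicting denominators, and under either one entry depends on steps the EDSS is meant to change

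*Protocol article*

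**What the plan says.** The protocol article describes this outcome twice.

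- **Outcomes, Secondary outcomes:** "Proportion of providers who took the appropriate action per participant (as recommended by the mIRA EDSS) in response to the aforementioned symptoms" (six are listed) "or reported clinical parameters indicative of PIH, GDM, or severe anaemia".
- **Data collection, Table 1, secondary outcome #3:** the outcome is taken "among participants who said they were experiencing vomiting, vaginal bleeding, severe headache" and the other listed symptoms, "or who were told that they had hypertension in pregnancy, GDM or anaemia) the action taken by the provider in response".

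Other parts of the article bear on who enters these denominators (outcome numbers follow Table 1):

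- Symptoms discussed, whether the provider asks or the woman mentions them, are outcome #2.
- Being "told by the provider that they had PIH, GDM or severe anaemia" is outcome #5, and recorded diagnostic parameters are outcome #6.
- Performing the tests that produce those parameters is the primary outcome.
- The Aims section makes better identification and communication of these conditions an objective, to be compared between arms.
- The Statistical methods section gives a log-link GEE for categorical secondary outcomes and names only #5 and #6.

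**The concern.** There are two linked problems.

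First, the definitions select different women. One uses a clinical parameter, the other what the woman was told. One says severe anaemia, the other anaemia without qualification. A reader cannot tell which will be analysed.

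Second, both conditions for entry arise after randomisation, through provider behaviour that the intervention targets. If the EDSS works, more women enter its denominator, and they may differ from those who enter under usual care. Randomisation then no longer protects the comparison of the two conditional percentages. A difference could reflect who was found, not how well providers responded.

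**Working it through.** **Step 1. The two definitions side by side**

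| Feature | Secondary outcomes section | Table 1 |
|---|---|---|
| Condition trigger | reported clinical parameter | told of the condition |
| Anaemia | severe | no severity stated |
| Symptom trigger | six listed symptoms | the same six, voiced by the woman |
| Qualifying value recorded, not told, no listed symptom | counted | dropped |
| Never tested, no listed symptom | not counted | not counted |

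The severity wording could matter. The Study design and setting section says more than half of pregnant women in the state are anaemic. If that held here, more than 0.5 × 660 = 330 women per arm could be candidates under the Table 1 wording if all were tested and told. The document gives no frequency for severe anaemia, so the gap cannot be sized.

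**Step 2. What selection alone can do**

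The article gives no figure for this outcome, so there is nothing to reproduce. The only input from the document is 660 women per arm (Sample size). The rest are assumptions, identical in both arms unless stated:

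- 20% have a qualifying problem: 660 × 0.20 = 132. Of these, 30% are overt (39.6) and 70% subtle (92.4).
- Overt problems are detected with probability 0.9: 39.6 × 0.9 = 35.64.
- Subtle problems are detected with probability 0.2 in control, and d = 0.2, 0.4, 0.6 or 0.8 with the EDSS.
- Once a problem is detected, action is appropriate with probability 0.9 (overt) or 0.5 (subtle).

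Formulas:

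- Denominator D = 35.64 + 92.4 × d
- Numerator N = 35.64 × 0.9 + 92.4 × d × 0.5
- Conditional proportion = N/D; all-women proportion = N/660

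Control (d = 0.2): D = 35.64 + 18.48 = 54.12; N = 32.076 + 9.24 = 41.316; N/D = 0.763.

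| EDSS d | D | N | N/D | Conditional RR | All-women RR |
|---|---|---|---|---|---|
| 0.2 | 54.12 | 41.316 | 0.763 | 1.00 | 1.00 |
| 0.4 | 72.60 | 50.556 | 0.696 | 0.91 | 1.22 |
| 0.6 | 91.08 | 59.796 | 0.657 | 0.86 | 1.45 |
| 0.8 | 109.56 | 69.036 | 0.630 | 0.83 | 1.67 |

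Providers act equally well within each case type, so only the case mix moves the conditional ratio.

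**Step 3. The direction is not fixed**

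- *Newly found cases easier to act on.* Swap the action rates (0.5 overt, 0.9 subtle). Control: N = 17.82 + 16.632 = 34.452, N/D = 34.452/54.12 = 0.637. EDSS at d = 0.8: N = 17.82 + 66.528 = 84.348, N/D = 84.348/109.56 = 0.770. Conditional RR = 0.770/0.637 = 1.21, now favouring the EDSS although action within each type is still equal.
- *Same action rate for both case types.* The conditional RR is 1.00 at every d.
- *EDSS also improves action in subtle cases, from 0.5 to 0.6, with d = 0.8.* N = 32.076 + 44.352 = 76.428. Conditional RR = (76.428/109.56)/0.763 = 0.91; all-women RR = 76.428/41.316 = 1.85.

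**The case against.** The strongest reply is that a conditional measure of response is a defensible choice. The objective concerns the quality of the provider's response, and detection is already covered by the primary outcome and by outcomes #2, #5 and #6. An all-women measure mixes detection with response and gives a woman without any problem the same score as one who was mismanaged. Table 1 is presented as a summary, and the analysis set may be fixed in a SAP that is not shown. This supports keeping the conditional percentage as a description. It does not restore comparability between arms, and it does not remove the contradiction between two current parts of the article.

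Some stronger readings are tempting, but the documents do not support them:

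- *The outcome will make a successful EDSS look worse, because control contains only obvious cases.* Nothing in the article gives the case mix, and Step 3 shows the bias can go either way or be nil.
- *The Secondary outcomes section takes the provider as the unit.* The phrase reads "Proportion of providers who took the appropriate action per participant (as recommended by the mIRA EDSS", and the words on the participant largely point to the woman. The wording is loose, not a clear conflict.
- *Women who are missed disappear from the trial.* Untested women count against the primary outcome, and women with a recorded value who were not told show up when outcomes #5 and #6 are compared.
- *The economic evaluation repeats the flaw.* It lists the proportion identified and, separately, "the proportion of women with GDM or PIH whose blood sugar and pressure are controlled to recommended targets". The second phrase is not restricted to identified women, and the two are distinct inputs.

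**Conclusion.** The point holds for this one secondary outcome. The inconsistency in trigger and anaemia severity is plain in the text and needs no assumption. It also follows from the text that entry to either denominator depends on processes the EDSS targets, so randomisation does not protect the comparison of conditional proportions.

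The size and direction of any bias cannot be derived from the documents. The shift in the conditional risk ratio from 1.00 to about 0.83, against an all-women ratio of about 1.67, is an illustration. It rests on assumed prevalence, detection and action rates, and on subtle cases being harder to act on. The primary outcome and the sample size are unaffected.

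**What to change.** 1. Reconcile the Secondary outcomes section and Table 1 to one trigger, including the anaemia severity, and state the woman as the unit.
2. Make the between-arm comparison over all enrolled women: 1 if a qualifying symptom or parameter was found and the appropriate action taken, otherwise 0. State how a woman whose second visit is not observed is scored, since the article's missing-data rule is written for the primary outcome.
3. Extend to this outcome the log-link GEE that the article states for the other categorical secondary outcomes. At present it names only #5 and #6.
4. Report the conditional percentage descriptively, with its numerator and denominator by arm.

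The cost is a change of wording in the protocol and SAP. No new data are needed, because the observation checklist and the Mother and Child Protection cards are already planned for all enrolled women in both arms. The drawback is that the all-women measure gives a lower percentage and mixes detection with action, so both parts should be tabulated beside it.

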**Fig. 5 Fig5:**
[figure not shown]
CONSORT Trial flow diagram

### Statistical methods

The primary analyses will be conducted according to randomised arm of the facility in which pregnant women were recruited. The continuous primary outcome (i.e. mean number of the four selected components of ANC observed over two visits) will be analysed at the individual level using Generalised estimating equation (GEE) analysis with identity-link function. GEE assumes that observations within the same clusters may be correlated. For the analysis of cluster randomized trials, it is usual to assume that the correlation matrix is exchangeable, meaning that observations on participants in different clusters are uncorrelated, while observations on individuals in the same cluster all have the same correlation coefficient ρ.

We will adjust the primary analysis regression for the following pre-specified baseline covariates likely to be associated with the outcome to improve the efficiency of the analysis and avoid chance imbalances [35]: gestational age at enrolment, number of previous ANC visits and scheduled caste or tribe.

For categorical secondary endpoint analyses i.e., the proportion of pregnant women who were told by the provider that they had hypertension in pregnancy, GDM or severe anaemia and proportion of pregnant women for whom there was a recording of the diagnostic parameters of hypertension, GDM or severe anaemia, the relative risk for these secondary outcome(s) between the mIRA EDSS and standard care group will be analysed at the individual level using GEE analysis with logarithmic-link function.

Recognising that the trial is not powered to detect effect differences in subgroups, we will conduct exploratory subgroup analyses for the primary outcome to determine if the intervention effect varies by the following pre-specified subgroups: age (split at the median); parity (0/1 or more); caste or tribe (yes/no); highest education level completed (completed primary or above/other); EDSS use (used for entire ANC consultation/not used for entire consultation) and gestational age at first visit (< 10 week/10 week or above). Within the pre-specified subgroups, we will assess heterogeneity of treatment effect with a test for interaction [5–9]. Interaction test p-values will be presented but will be interpreted with caution, due to the exploratory nature, the multiple tests performed and the low power of the interaction test. We will estimate beta coefficients along with 95% CIs for each subgroup. As this is an exploratory analysis of potentially influential characteristics, we will not hypothesise effect directions.

The primary outcome data with missing values will be handled under two different assumptions. First, the primary outcome will be considered as complete if it is confirmed that the participant attended the facility for the second visit. Data missing for both of these visits will be assumed and coded as component ‘not done’. Second, the primary outcome will not be considered as complete if the second visit data is missing and it is confirmed that the participant did not attend for this visit. In this case, participants’ data will not be included in the primary analysis.

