### Cluster randomization

Sixty-six clusters will be randomly assigned to either the control or intervention group with a 1:1 allocation ratio via a computer-generated randomization schedule stratified by district (33 clusters in each arm). Randomization units will be clusters of three health facilities–a PHC and two linked SCs. Cluster randomization was preferred over the individual randomization to avoid contamination among the participants (pregnant women). Randomization will be performed by the trial statistician, who is not involved in the day to day running of the trial. Covariate constrained randomization will be used to balance the arms on the following baseline covariates: presence of a lab and lab technician (yes/no); more than three staff providing ANC (yes/no); facility type (PHCs that are always open/PHCs that are not).

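### The primary GEE leaves out district and the three cluster factors balanced by the randomisation, so its standard error is too large to the extent that those factors predict the outcome

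*Protocol article*

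**What the plan says.** Under Cluster randomization, the protocol article allocates 66 clusters 1:1 "via a computer-generated randomization schedule stratified by district", of which there are five. It adds: "Covariate constrained randomization will be used to balance the arms on the following baseline covariates: presence of a lab and lab technician (yes/no"), and then "more than three staff providing ANC (yes/no); facility type (PHCs that are always open/PHCs that are not"). Four cluster-level factors therefore shape the allocation.

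Under Statistical methods, the primary outcome "will be analysed at the individual level using Generalised estimating equation (GEE) analysis with identity-link function", with an exchangeable working correlation described as usual. The adjustment set is given as "gestational age at enrolment, number of previous ANC visits and scheduled caste or tribe". The stated reason is that these are "pre-specified baseline covariates likely to be associated with the outcome to improve the efficiency of the analysis and avoid chance imbalances". None of the four design factors is in this set, and no other section of the article adds them.

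**The concern.** Balancing a prognostic cluster factor by design removes its contribution from the sampling variance of the arm difference. A model that omits the factor still counts its variance as unexplained between-cluster variation. The reported standard error then exceeds the true one, the confidence interval is too wide, and the test rejects a true null less often than 5%. The precision bought by stratifying and constraining is not collected.

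This also sits badly with the article's own reason for adjusting, which is efficiency. In a trial with 66 clusters, a large part of the variance of a cluster mean lies between clusters (46% at the planning values, shown below). Cluster-level factors address that part most directly, yet all the chosen covariates are woman-level.

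**Working it through.** **Inputs from the Sample size section.** Difference 0.5 over two visits; SD 0.9 per visit, doubled to 1.8; ICC 0.05; 20 women per cluster; 52 clusters (1,040 women) for 90% power; 20% loss; 66 clusters (1,320 women) enrolled. With 20% loss, m = 16 analysed women per cluster and k = 33 clusters per arm.

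**Assumptions.** Two-sided alpha of 0.05. R is the share of between-cluster variance explained by the four factors; the documents do not give it, so 0 to 0.5 is shown.

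**The plan's own figure.** n per arm = 2(1.96 + 1.2816)² × 1.8² / 0.5² ≈ 273. The design effect is 1 + 19 × 0.05 = 1.95, and 273 × 1.95 ≈ 532 against 520 stated. Power at 520 per arm is 89.4%. For loss, 1,040/0.8 = 1,300 women = 65 clusters, or 66 for equal arms. The plan's figure reproduces closely.

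**Effect of the omission at ICC 0.05.**
- Between-cluster variance: 0.05 × 3.24 = 0.162. Within-cluster variance: 3.078, so 3.078/16 = 0.1924 per cluster mean.
- Between-cluster share of a cluster mean's variance: 0.162/0.3544 = 46%.
- Reported SE without the factors: √(2 × 0.3544/33) = 0.147, whatever R is.
- True SE when the factors are balanced: √(2 × [0.162(1 − R) + 0.1924]/33).
- Type I error without the factors: 2[1 − Φ(1.96 × SE reported / SE true)].
- Power without the factors: Φ((0.5 − 1.96 × SE reported)/SE true). Power with them: Φ(0.5/SE true − 1.96).

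| ICC | R | SE reported | SE true | Type I error, factors omitted | Power, omitted | Power, included |
|---|---|---|---|---|---|---|
| 0.05 | 0 | 0.147 | 0.147 | 5.0% | 92.7% | 92.7% |
| 0.05 | 0.3 | 0.147 | 0.136 | 3.5% | 94.1% | 95.7% |
| 0.05 | 0.5 | 0.147 | 0.129 | 2.6% | 95.1% | 97.3% |
| 0.10 | 0 | 0.175 | 0.175 | 5.0% | 81.4% | 81.4% |
| 0.10 | 0.3 | 0.175 | 0.157 | 2.9% | 84.0% | 88.8% |
| 0.10 | 0.5 | 0.175 | 0.144 | 1.8% | 86.1% | 93.3% |

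The ICC 0.10 rows use the same formulas with variances 0.324 between and 2.916/16 = 0.1823 within. That ICC is a sensitivity value, not one from the documents.

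**Simulation check** (66 clusters of 16, five strata, allocation drawn from the best-balanced candidates). At ICC 0.05 and R of 0.3 to 0.5, type I error without the factors was 2.8% to 3.8%. Power at 0.5 rose from 93–95% to 95–97% on adjustment. At R = 0, power was 92.6% without and 92.4% with the factors. At ICC 0.10, with a t reference, power rose from 81.8% to 86.9% at R = 0.3 and from 83.9% to 92.4% at R = 0.5. Closed form and simulation together put the loss at ICC 0.10 at roughly 5 to 8 points.

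**The test matters once the factors are added.** With equal clusters and no woman-level covariates, an exchangeable identity-link GEE reduces to cluster means with a sandwich variance. Using an uncorrected sandwich SE and a z reference at ICC 0.05, type I error was 5.5% (R = 0) and 4.8% (R = 0.3) without the factors, and 6.9% and 7.8% with the seven extra terms. A small-sample correction restored 4.7% to 4.9%.

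**The case against.** Several counter-arguments have force.

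- **Size.** At the planning ICC the loss is about 2 points, and power is already above 90% without the factors. The sample size took no credit for stratification, so the omission does not push the trial below plan. This stands. A reader might infer that the trial is underpowered because of the omission; the figures do not support that. At ICC 0.10 power would be 81.4% even at R = 0, which is a consequence of the ICC.
- **Unknown R.** The loss exists only if the factors are prognostic, and the documents give no figure. This stands, and the conclusion is conditional on it. It is tempting to call a laboratory a direct determinant of three of the four primary components, but the article does not show this. Women are also observed at sub-centres, one component is a dipstick, and glucometer values are provided for. The formative work found mostly adequate infrastructure, yet urine and blood glucose tests were often missed. The text supports plausibility only: three components are tests, and the districts were chosen to include some with low levels of adequate ANC.
- **The remedy can do harm.** With an uncorrected sandwich z-test, adding seven terms turns a near-nominal test into an anti-conservative one. This stands and changes the fix.
- **Condensed article.** The Blinding section mentions a separate statistical analysis plan, which may deal with the strata. That would settle the matter in practice. But the article does not leave the primary covariate set open: it names one, and that set omits the design factors.

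**Conclusion.** The point holds in a limited, conditional form. The stated primary model ignores the four factors that shaped the allocation. If they explain 30% to 50% of between-cluster variance, the reported SE is about 8% to 14% too large (0.147/0.136 to 0.147/0.129). At ICC 0.05 the test then runs at about 3% to 4% and forgoes about 2 points of power at a difference of 0.5; at ICC 0.10 the loss is roughly 5 to 8 points. If they explain nothing, nothing is lost.

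The omission does not bias the estimate, and it makes the test conservative, so a reader should not infer a risk of false-positive findings from it. The omission itself is certain from the text; its size rests on the assumed R, equal cluster sizes and no contribution from the woman-level covariates. It is worth correcting because correction is cheap, not because the trial's validity is threatened.

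**What to change.** Amend the covariate sentence under Statistical methods, and the statistical analysis plan if it says the same, before the analysis team is unmasked:

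- Add district (four indicators), laboratory and technician, more than three ANC staff, and always-open PHC as fixed effects in the primary GEE, beside the three covariates already listed.
- Specify a small-sample-corrected robust SE and a t reference on cluster degrees of freedom: 66 minus nine cluster-level parameters (intercept, arm, four district terms, three binary factors) = 57. The added terms should not go in without this.
- Keep the model without the four factors as a sensitivity analysis.
- Do the same for the other continuous outcomes. In the log-link secondary models, include the factors only where the model converges.

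The cost is wording. The variables must already be held for all 66 clusters, because the allocation uses them. The statistical price is about seven cluster-level degrees of freedom, which is under 2 points of power if the factors turn out not to be prognostic (92.6% against 92.4% in simulation at ICC 0.05).
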